### The value of digital technologies for Parkinson’s disease assessment

1.6

Classical objective tests for the assessment of PD include neuroimaging or analysis of blood or cerebrospinal fluid (CSF) (70–72), but these are generally invasive and can be costly. In addition, they may not be accessible in every setting or may require specialist knowledge to undertake. Portable, digital methods for assessment offer a valuable alternative that can potentially improve delivery of, and access to, clinical care. Importantly, digital technologies may be of particular value in LMICs to improve healthcare delivery where human and financial resources are limited (73). While there may be challenges associated with the introduction of these new technologies into existing workflows and healthcare systems in LMICs (74), there is now considerable evidence of their feasibility and utility in clinical use, in particular allowing remote assessment and collection of data (75, 76). Mobile phones are now widely used in most countries around the world which allows easier connectivity between citizens and healthcare providers, particularly in remote rural areas (77). In fact, one of the key learnings from the COVID-19 pandemic, particularly for LMICs, was that embracing digital technologies has the potential to not only improve the ability to respond to public health challenges but can also strengthen primary healthcare systems delivering care (78).

Digital tools and other innovative technologies are already widely used in the fields of neurology and movement disorders to assist clinicians with diagnosis, monitoring and treatment decisions, and continue to be the focus of considerable research and development (12, 79–82). Smartphone applications and smartwatches, along with machine learning technology, are being increasingly used to collect activity data that can aid the diagnosis and monitoring of PD (83–87). They have also been evaluated for use in gathering outcomes data in clinical trials (88). Smartphones are relatively easy to use, familiar to most people, relatively low cost, non-invasive and allow data collection by non-specialists, either in-person or remotely. The various sensors that are typically incorporated in smartphones, such as accelerometers, gyroscopes, microphones, make them ideally suited for gathering information from people with PD. Testing activities for PD diagnosis using smartphone applications have been used successfully and with good accuracy for analysis of gait (89, 90), spoken voice (91, 92) and tremor (93, 94). Finger movement while typing has also shown promising results with high accuracy for the early detection of PD (95, 96). Data gathered from these activities by the smartphone’s sensors are processed for extraction of diagnostic features, which can include general statistical analyses (mean, standard deviation, percentiles), but also measurements of time and frequency. The extracted features are then fed into a machine learning classifier, such as neural networks (NN), decision tree, and support vector machine (SVM), to distinguish between PD and non-PD cases (90, 92, 97). Mobile technology and the use of digital markers has recently been successfully validated for the self-administered, at-home assessment of Alzheimer’s disease risk to allow remote screening to support clinical assessment (98). Another digital strategy that is currently being evaluated in a clinical trial in people with Alzheimer’s disease (NCT05027789), is what is termed a “Brain Boosters” intervention, which combines memory training and promotion of healthy lifestyle behaviors which are implemented and monitored using a digital application (99).

The research team at ChulaPD has extensive experience in the field of digital technologies, with a track record of publication on device/sensor development and applications (96, 100–104). To date, the devices and technologies that have been developed have been focused on strategies for patients who have already been diagnosed with PD. They have been employed to improve the accuracy of PD diagnosis and monitoring and to help inform suitable therapeutic interventions, as well as being used as assistive technologies to aid intractable symptoms such as freezing of gait using a laser cane (105), intractable tremor using the specially-designed “Tremor’s Glove” (106), and for assessment of nocturnal hypokinesia with nocturnal devices.

Recognizing the importance of early detection of PD, the team has applied their digital expertise to the Parkinson’s disease risk survey in order to develop screening strategies for the Thai population that can detect subtle symptoms and undertake risk evaluation. They have developed a smartphone application that collects tremor, gait, finger tapping and voice data to detect early signs of PD and incorporates newly developed speech tests using Thai sentences and sustained vowels, along with a finger pinching test. The process for selection and validation of these digital markers is described in Methods, section 2.3.

Thailand is an example of a small LMIC that has benefitted from considerable social and economic development in recent decades, and has an established program of universal healthcare in place for its citizens (12). These attributes make it well placed for implementation of a national screening program using digital technology, as it proposed for the Parkinson’s disease risk survey. In addition, due to national distribution by the Chula PD team of the laser cane device that helps identify moderate-to-advanced stage PD patients with gait problems, there is already an existing clinical network that can be used to assist in identification of patients in the early stage of PD.

### The Thai Parkinson’s disease risk survey

1.7

The Parkinson’s disease risk survey (Thai Clinical Trials Registry identification number: TCTR20231025005) is being undertaken to evaluate a digital population screening platform that will allow identification of undiagnosed cases of PD, which may include early and more advanced cases, within the Thai population aged over 40 years. It is also hoped that the study will identify those in the prodromal stage as well as at-risk individuals who can be targeted with preventive lifestyle interventions. The overall rationale and objectives of the national digital screening program and its expected outcomes are outlined in Figure 2.

**Figure 2 fig2:**
[figure not shown]
Rationale and objectives of the Parkinson’s disease risk survey screening program.

The Parkinson’s disease risk survey project has been implemented in collaboration with the Thai Red Cross Society and is celebrated under the auspicious occasion of [name], Executive Vice President of the Thai Red Cross Society. The design of the study involved collaboration between a multidisciplinary group of experts in the field of PD, comprising movement disorders neurologists, led by RB, project manager, general neurologists, internists, data science engineers with experience in machine learning, PD nurse specialists, patient representatives, a physical therapist, a dietitian, and policymakers. The campaign was officially opened on the 18th of January 2024 by the Princess on the occasion of the implementation of the first field study in Nakhon Sawan Province, located in the north-central part of Thailand (Figure 3).

**Figure 3 fig3:**
[figure not shown]
The Parkinson’s disease risk survey project implemented in honor of [name], Executive Vice President of Thai Red Cross Society. Top: Her Royal Highness and the multidisciplinary team involved in the study’s design, validation, and implementation at the official opening event; bottom: subjects being screened with the digital tools.

Prodromal PD refers to the stage at which individuals do not fulfill diagnostic criteria for PD (i.e., bradykinesia and at least one other motor sign) but do exhibit signs and symptoms that indicate a higher-than-average risk of developing motor symptoms and a diagnosis of PD in the future (62). The digital platform will be deployed nationally and allow the collection of data on the person’s speech, hand tremor, finger dexterity, and mobility, which will be analyzed alongside information obtained from a questionnaire about PD symptoms completed by the participants. The outcomes will enable a range of lifestyle interventions to be implemented in those determined to be at risk of developing PD in the future or suitable treatment for those considered to have early PD.

Evidence is emerging that interventions such as regular exercise, consuming a more Mediterranean-style diet, and ensuring adequate sleep quality can potentially help slow disease progression and the transition from the prodromal stage to clinical PD. Once subjects who may have prodromal have been identified through national screening (Phase 1 of the project), these lifestyle interventions—namely EAT, MOVE and SLEEP—can be implemented subsequently on a personalized basis with the objective of preventing or minimizing the development of PD within Thailand (Phase 2 of the project) (12). It is anticipated that this digital platform could also act as a model for similar screening strategies for other non-communicable diseases in Thailand.

This manuscript describes the overall design and implementation of Phase 1 of the Parkinson’s Disease Risk Survey study in Thailand, including the development and validation of the questionnaire and markers that comprise the digital platform, and the procedure for extraction and analysis of the data using machine learning tools that will identify subjects at risk of developing, or with early signs of PD. The study is currently in the early stages of implementation based on this validated methodology, and participants’ data are being collected and analyzed on an ongoing basis, and will be reported separately in due course.

## Methods and analysis

2

### Overall study design

2.1

The Parkinson’s disease risk survey aims to target all Thai citizens above 40 years of age. The survey will be implemented in three ways: (1) individual citizens can download the app and complete the questionnaire and tests themselves, (2) field studies will be undertaken by the ChulaPD research team across different provinces in collaboration with provincial public health offices, provincial hospitals, provincial Red Cross chapters, and district Red Cross branches, and (3) digital screening stations will be set up in every provincial hospital across Thailand. The composition of the assessment package that comprises the digital platform is shown in Table 1.

**Table 1 tab1:** Composition of the digital assessment package for national Parkinson’s disease screening in Thailand.

Test	Description	Program picture	
Questionnaire (yes or no)	10 motor symptom questions 5 nonmotor and prodromal symptom questions 5 atypical parkinsonism/red flag symptom questions	[figure not shown]	
**Voice analysis**			
Phonation	Ask participant to say the word “Ah” loudly for 10 s.	[figure not shown]	
Prosody and articulation	Ask participant to say the sentence “ยายพาหลานไปซื้อขนมที่ตลาด.”	[figure not shown]	
**Motor analysis**			
Tremor tests	Rest tremor (put the device on the participant’s hand while it is resting on their lap for 20 s) Postural tremor (the participant holds the device in their hand with their arm outstretched against gravity for 20 s) *Measure the tremor of both hands but one hand at the time*	[figure not shown] Rest tremor	[figure not shown] Postural tremor
Alternate finger tapping	Ask the participant to alternately tap with the index and middle fingers as fast as possible for 10 s. *Test both hands but one hand at the time*	[figure not shown]	
Pinch-to-size test	Ask the participant to pinch the finger to match the different sizes of the circle shown on the screen 5 times. *Only test the dominant hand*	[figure not shown]	
Gait test	Ask the participant to put the device in their pocket and walk straight for 3 meters, turn around and then walk back.	[figure not shown]	
Balance test	Ask the participant to put the device in their pocket and stay completely still for 15 s.	[figure not shown]	

Subjects who participate in the national screening study will be asked to give written informed consent before the enrolment in accordance with the declaration of Helsinki (IRB No.0804/65). They will be asked to complete a validated 20-item questionnaire (see below for details of its development and validation) to determine if they are experiencing any motor or nonmotor PD symptoms or if there are any signs of atypical parkinsonian disorders. They will also undertake objective tests to measure their performance on specific motor tasks, comprising spoken voice, tremor, dexterity, and mobility (see below for details of their selection and validation). Tests will be performed, and data collected, using mobile smartphone technology.

Data collected via the digital platform is stored in a database created and managed by the Thai Red Cross Society, strictly in accordance with the relevant Institutional Review Board and Personal Data Protection Act regulations. The Thai Red Cross Society is a major national non-profit public organization that undertakes humanitarian activities, including those related to the promotion of quality of life and disease treatment and eradication, in keeping with the principles of the International Red Cross. The Society is closely affiliated with ChulaPD, the only tertiary center in Thailand dedicated to the study and care of PD, with whom they have collaborated over many years on national projects related to PD and its management (28, 107).

Identification of individuals who may have undiagnosed PD (both early and more advanced), those who may be in the prodromal stage, or those at risk of developing the condition will be evaluated by different machine learning models using combined data from the questionnaire and objective measurements.

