#### Digital marker validation and data analysis

2.3.2

The eight selected markers have been developed into a digital application that has been validated as described below. Validation was undertaken in a cohort of 343 people with PD (48.6% male) and 230 control subjects (27.9% were male) without PD. Participants undertook each test activity using a mobile application and data were recorded using the built-in sensors of the mobile phone, namely the accelerometer, gyroscope, microphone, and touch screen. The validation study was approved by the Human Ethics Committee of the Faculty of Medicine, Chulalongkorn University (IRB number 0804/65). All subjects gave written informed consent before the enrolment into the study, in accordance with the declaration of Helsinki. Performance on the eight test activities were recorded by each participant using a mobile application and the built-in sensors of a smartphone, namely the accelerometer, gyroscope, microphone, and touch screen. Details of how each testing activity was performed is described in Table 5.

**Table 5 tab5:** Performance methods for each of the digital marker test activities.

Marker	Description of test
Voice vowel	Participants pronounce the sustained vowel /a/, as in “*bar*,” for 10 s without holding their breath. The test is repeated three times for each participant.
Voice sentences	Participants read sentences aloud in the Thai language, such as the example sentence “*rod tid mak loey*,” which means “*The traffic is really jammed*.” The test includes a total of 25 sentences that are commonly encountered in real-life situations.
Resting tremor	Participants are instructed to place the mobile phone on one palm with the screen facing up and lay their hand in their lap. They are then asked to specify whether the device is on the left- or right-hand side by pressing on the screen. Finally, participants are instructed to keep their hand still, along with the device, for 20 s.
Postural tremor	Participants are instructed to hold the device and press on the screen to verify which side of the hand they are holding, then stretch out their arm and maintain that posture for 20 s.
Alternate finger tapping	Participants place the device on a flat surface. They are then instructed to use their index and middle fingers of one hand to tap on two circles that appear on the screen, alternating between the two fingers as quickly as possible while maintaining correct finger alternation within 10 s.

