Pinch-to-size	Participants place the device on a flat surface. They are instructed to use their thumb and index finger of one hand to pinch, following the varying size of a circle that also moved randomly across the screen. The test is repeated five times for each participant.
Gait	Participants hold the device and walk in a straight line for 3 meters, then turn around and walk back to the starting position. The route for testing is set up to indicate the walking direction and the turning point.
Balance	Participants are instructed to put the device in a pocket after pressing start to begin the test. They then stand still for 30 s. A tone is played to signify the end of the test.

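### Tables 1 and 5 disagree on balance time, gait phone position and sentence content, so the validation accuracy is not shown to apply to the battery being deployed

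*Protocol article*

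**What the plan says.** Table 1 in section 2.1 gives the composition of the national screening package. Table 5 in section 2.3.2 gives the procedures used in the validation cohort of 343 people with PD and 230 controls.

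- **Balance.** Table 1: "Ask the participant to put the device in their pocket and stay completely still for 15 s". Table 5: "They then stand still for 30 s".
- **Gait.** Table 1: "Ask the participant to put the device in their pocket and walk straight for 3 meters, turn around and then walk back". Table 5: "Participants hold the device and walk in a straight line for 3 meters, then turn around and walk back to the starting position".
- **Voice sentence.** Table 1: "Ask participant to say the sentence", followed by a single Thai sentence. Table 5: "The test includes a total of 25 sentences that are commonly encountered in real-life situations", with a different sentence as its example.

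The validation results are then carried over to the deployed tool. Section 1.7 states: "The study is currently in the early stages of implementation based on this validated methodology". The end of section 2.3.2.5 treats the results as confirming the application and testing system, and the last paragraph of the Discussion calls the platform a validated, highly accurate method for national screening.

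**The concern.** A classifier's AUC and accuracy belong to the classifier together with the way its inputs were acquired. Section 2.3.2.1 describes the inputs as summary statistics (mean, SD, kurtosis, skew) and time- and frequency-domain features of the recorded signal. Such features can depend on recording length, sensor position and, for speech, what is spoken. For gait there is a specific reason to expect some dependence: a phone in the hand moves with the arm, a phone in the pocket does not, and the questionnaire (Table 2) treats reduced arm swing as a motor sign of PD.

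If both tables are accurate, a forest trained on one kind of recording would be scored on another, and the published performance would have no demonstrated link to the tool in use. Model output matters here: people flagged with early signs are referred to a neurologist, and those classed as prodromal are to be targeted in Phase 2. The survey is aimed at all Thai citizens above 40, and data collection has begun.

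**Working it through.** The reported accuracy cannot be recomputed, because the article gives no confusion matrix or individual data. The check is a line-by-line comparison, a count of how much of the reported performance rests on the affected tests, and a test of whether Table 4 can settle the points left open.

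**1. Table 1 against Table 5**

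| Test | Table 1 (deployed) | Table 5 (validation) | Reading |
|---|---|---|---|
| Balance | pocket, 15 s | pocket, 30 s | contradiction; 15/30 = 0.5 of the time |
| Gait | phone in pocket | phone held | contradiction |
| Voice sentence | one fixed sentence | 25 sentences | contradiction |
| Voice vowel | 10 s, repeats not mentioned | 10 s, three repeats | Table 1 silent |
| Tremor, tapping | both hands in turn | described for one hand | wording only |
| Pinch-to-size | dominant hand, five times | one hand, five times | wording only |

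Durations for the vowel (10 s), tremor (20 s) and tapping (10 s) agree, as does the gait path. The gait difference is hard to put down to loose wording: in the next row Table 5 places the phone in a pocket for balance, so it distinguishes the two positions.

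**2. How much reported performance depends on the three tests**

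Table 6 gives single-test AUCs of 0.88 (balance, the highest), 0.84 (gait) and 0.83 (voice sentences). These are three of its nine rows.

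Ticks across the eight combinations in Table 7:

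- balance: 8 of 8
- gait: 7 of 8 (absent only from the five-test set of questionnaire, sentence, vowel, postural tremor and balance)
- voice sentences: 4 of 8

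The best set (accuracy 0.9108, SD 0.012357) is questionnaire, vowel, rest tremor, gait and balance, so it contains two of the three contradicted tests. Because balance is in every row, each accuracy listed, from 0.9018 to 0.9108, rests on at least one test whose deployed procedure differs from the validated one.

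**3. Can Table 4 settle hands or repeats?**

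Section 2.3.2.3 reports 162 people with PD and 128 controls who completed all tests. Minimum recordings expected from completers, against the totals in Table 4:

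- two hands for each tremor test: 162 × 2 = 324 against 211; 128 × 2 = 256 against 154
- three vowel repeats: 162 × 3 = 486 against 315; 128 × 3 = 384 against 183
- 25 sentences: 162 × 25 = 4050 against 512; 128 × 25 = 3200 against 331

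The counts fall short even where Table 5 states the repeats outright. Either a recording in Table 4 is not one repeat or one hand, or Table 5 was not followed literally. Table 4 therefore cannot show which hands were tested.

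**The case against.** Several points on the other side are fair.

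- **One table may simply be misdescribed.** The pictures in Table 1 and Figure 4, which might show phone placement, were not in the text available for review. If so, the repair is a text correction. This stands, and the fix allows for it.
- **The sentence difference is the softest of the three.** Section 2.3.1.1 speaks of sentences in the plural for the deployed platform, the 25 may be a pool, and the sentence test is not in the 0.9108 set. This stands as a limit on its weight; the two tables still disagree.
- **The validation forest may not be used unchanged.** Section 2.1 mentions different machine learning models, and the Discussion expects continued training. Neither mentions a change in acquisition, so this softens the consequence without removing the inconsistency.
- **Referral to a neurologist limits the harm of false positives.** True, but it does nothing for missed cases.

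Three stronger readings are tempting and are not supported. A reader might take Table 1's "Measure the tremor of both hands but one hand at the time", set beside Table 5's one-hand wording and the 211 tremor recordings, as proof that validation used one hand only. Table 5 has participants record which side is being tested, which fits two recordings in sequence, and the counts are uninformative for the reason shown. A reader might count vowel repeats as a difference, but Table 1 is only silent. A reader might compute a variance inflation from the shorter balance recording or from fewer vowel trials. That would require time-averaged features from stationary, roughly independent data, or averaging over trials, and the article states neither.

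**Conclusion.** The point holds for three contradictions: balance time, gait phone position and sentence content. Confidence is high that the tables disagree and that the article does not acknowledge it. All eight ensemble accuracies in Table 7, and the AUCs for balance, gait and voice sentences in Table 6, were obtained under the Table 5 procedures and are not shown to apply under those of Table 1.

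It would go too far to say that the figures do not apply, or that scores shift for everyone screened. The article holds nothing from which the size or direction of a change could be derived, and performance might prove similar. The conclusion assumes only that Table 1 describes what is deployed and Table 5 what was validated, as each is presented. It matters because the article tells readers that the platform being rolled out is validated with high accuracy.

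**What to change.** Reconcile the two tables and say which procedure was used where.

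1. **If one table is misdescribed**, correct it. This costs a text change.
2. **If both are accurate**, take one of two routes.
   - Align the Table 1 acquisition instructions with Table 5, so that the reported figures refer to the deployed procedure.
   - Or re-estimate Tables 6 and 7 under Table 1 conditions from stored recordings, where these exist: balance cut to its first 15 s, and the deployed sentence only if it was recorded. Pocket gait cannot be recreated from held-phone data. For gait, use the validated phone position, or report ensemble accuracy without gait until pocket gait has been validated.
3. **Until this is done**, state that accuracy under Table 1 conditions is unverified, and flag field data by acquisition version so that recordings made under different instructions can be separated.

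The cost is some re-analysis, a change of instruction text and a version variable in the database. Whether raw recordings were kept is an assumption. The re-estimated accuracies may be lower than those now reported.
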